### Data analysis

#### Analysis of pupil outcomes

The primary analysis will examine the association between pupil mental well-being and school policy type (restrictive/permissive). Multilevel linear models will be developed, accounting for repeated measures, clustering of classes and schools and adjusting for the school-level variables included in the propensity score estimations alongside relevant individual-level sociodemographic variables. Secondary analyses will use the same modelling approach investigating differences in the secondary (behavioural and mental health) and intermediary (smartphone and social media use) outcomes between school policy groups. Differential association between school policy and the primary, secondary and intermediary outcomes will also be explored across: (1) socioeconomic position; (2) gender; and (3) ethnicity by including relevant interaction terms in the developed models.

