### Sampling and participants

To improve the comparability of the two school groups, stratified sampling based on propensity scores was employed.^57^ We obtained routine data from the Department for Education on the following school characteristics: region, school type, urban or rural, total pupil roll size, Income Deprivation Affecting Children Index (IDACI),^58^ inclusion of a sixth form, selective or non-selective admissions policy, religious affiliation and the proportion of pupils with the following characteristics: male, from BAME groups, English as an additional language, eligible for free school meals and special education needs. Propensity scores were calculated using restrictive or permissive school smartphone policies as the outcome and school characteristics as explanatory variables. Propensity score terciles were then used to create three groups with subsequent division by restrictive or permissive policy type, resulting in six distinct sampling groups. Schools in each group have been randomly ordered and are being invited sequentially to participate, aiming to recruit six to seven schools from each restrictive tercile and three to four from each permissive tercile to achieve a sample size of 20 schools with restrictive and 10 schools with permissive policies.

In participating schools, two classes of mixed ability year 8 (age 12–13) and year 10 (age 14–15) pupils are recruited. We are focusing on adolescents in this age range because of the age of onset and prevalence of mental illness,^5^ and the prevalence of smartphone and social media use by adolescents aged 12–15.^7 14 59^ Within this age range we may also be able to observe potential differences in smartphone/social media use relationships with well-being.^33^ For example, year 8 pupils are likely to be newer users of phones/media and physical activity levels begin to decline at this age, particularly among girls.^7 13^ In year 10, pupils are more likely to be established phone/media users, mental well-being tends to be lower, and this age group are approaching the peak onset of mental health conditions.^4^ In addition to adolescent participants, the form teacher for each class recruited (or an equivalent teacher responsible for the class) and a member of senior leadership team (SLT) who is responsible for the school smartphone policy are recruited from each school.

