### Sample size calculation

To account for the imbalance of schools in our sample that have permissive (n=125) and restrictive policies (n=1220), we are recruiting schools using a 2:1 (restrictive: permissive) ratio. The primary outcome of mental well-being will be measured using the Warwick-Edinburgh Mental Well-Being Scale (WEMWBS; score range=14–70).^60^ To detect a mean difference in score of three points (considered the minimum clinically important difference^60^ between the two school groups), assuming a SD of 6.8^61^ and an ICC of 0.1 (a conservative estimate^62^), with 90% power and 5% significance, we require 20 schools in the restrictive and 10 schools in the permissive smartphone policy groups, with an average cluster size of 39 (1170 pupil participants in total; 780 in the restrictive, and 390 in the permissive policy groups).

In each participating class, we aim to recruit a minimum of 19–20 pupils (67% if estimated class size n=30). In studies with multiple layers of clustering (here classes within schools), it is conservative to treat clusters within clusters as one larger cluster, which is the approach used here.^63^

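### The stated 90% power belongs to an unadjusted comparison of 20 versus 10 schools, but the primary model spends about 17 school-level parameters on 30 schools

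*Protocol article*

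**What the plan says.** Under Analysis of pupil outcomes, the protocol article describes the primary analysis as multilevel linear models of mental well-being on policy type. They account for repeated measures and for clustering by class and school, and they are fitted while "adjusting for the school-level variables included in the propensity score estimations alongside relevant individual-level sociodemographic variables". The secondary and intermediary outcomes use the same approach.

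The variables are listed under Sampling and participants. The list begins "region, school type, urban or rural, total pupil roll size, Income Deprivation Affecting Children Index (IDACI" and continues with sixth form, selective admissions, religious affiliation and five pupil proportions (male, BAME, English as an additional language, free school meals, special educational needs). Study setting names six regions. The same variables produced the score used for sampling: "Propensity score terciles were then used to create three groups with subsequent division by restrictive or permissive policy type".

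Under Sample size calculation: "we require 20 schools in the restrictive and 10 schools in the permissive smartphone policy groups". The inputs are "To detect a mean difference in score of three points", "assuming a SD of 6.8", "an ICC of 0.1 (a conservative estimate" and "with 90% power and 5% significance", with an average of 39 pupils per school. That section makes no allowance for school-level covariates.

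**The concern.** Every pupil in a school has the same policy, so the policy effect is estimated between schools. The 1170 pupils make each school mean more precise but add no school-level degrees of freedom. Each school-level covariate uses one of those degrees of freedom and, in a small sample, overlaps with policy by chance, which widens the interval for the policy effect. The covariates recover precision only to the extent that they explain differences in well-being between schools.

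The sample size section and the analysis section therefore describe different comparisons. If the analysis is run as stated, the interval for the primary effect could be as wide as the 3-point difference the study is meant to detect, and a null result could not exclude that difference. The secondary and intermediary outcomes inherit the same school-level set.

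**Working it through.** **1. Reproduce the stated figure.** Inputs from Sample size calculation: difference 3, SD 6.8 (variance 46.24), ICC 0.1, 39 pupils per school, 2:1 allocation, 90% power, 5% significance (taken as two-sided).

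- Permissive pupils before clustering: (1 + 1/2) × (1.960 + 1.282)² × 46.24 / 3² = 81.
- Design effect: 1 + 38 × 0.1 = 4.8.
- 81 × 4.8 = 388.8 pupils; 388.8 / 39 = 9.97, so 10 permissive and 20 restrictive schools.
- Power at 390 and 780 pupils: 0.901.

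The figure is right for an unadjusted, normal-approximation comparison. A t test on 30 − 2 = 28 school-level degrees of freedom gives 0.880.

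**2. Count the school-level parameters.** Region 5 (six levels); school type, urban/rural, roll, IDACI, sixth form, selective admissions and religious affiliation 1 each (7); pupil proportions 5. Total q = 17. Residual school-level degrees of freedom: 30 − 2 − 17 = 11. The critical t rises from 2.05 to 2.20.

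**3. Standard error of the policy effect.** With R²y the share of between-school variance explained by the covariates, and R²x the share of policy explained by them:

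Var = [4.624 × (1 − R²y) + 41.616/39] × (1/10 + 1/20) / (1 − R²x)

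Here 4.624 = 0.1 × 46.24 and 41.616 = 0.9 × 46.24. If the covariates are unrelated to policy, the expected chance value of R²x is q/29. For q = 17 this is 0.586, a variance inflation of 29/12 = 2.42.

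- Unadjusted: √(5.691 × 0.15) = 0.92.
- q = 17, R²y = 0: √(5.691 × 0.15 × 2.417) = 1.44.
- q = 17, R²y = 0.3: √(4.304 × 0.15 × 2.417) = 1.25.
- q = 17, R²y = 0.5: √(3.379 × 0.15 × 2.417) = 1.11.

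The 95% half-width goes from 2.05 × 0.92 = 1.9 points to 2.20 × 1.44 = 3.2, 2.20 × 1.25 = 2.7 or 2.20 × 1.11 = 2.4.

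**4. Power at ICC 0.1.** The noncentral t formula fixes R²x at its expected value. Simulation lets it vary between samples (mean inflation about 2.7) and so gives slightly lower power.

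| School-level terms | R²y = 0 | 0.3 | 0.5 | 0.7 |
|---|---|---|---|---|
| 17, formula | 48% | 59% | 70% | 83% |
| 17, simulation | 48% | 57% | 68% | 79–80% |
| 13, formula | 62% | 74% | 83% | 93% |
| 13, allowing R²x to vary | 60% | 72% | 81% | 91% |

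The 13-parameter rows count region as one parameter. With 17 parameters, the formula reaches 90% at R²y of about 0.81; allowing R²x to vary requires somewhat more.

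**5. Lower ICC, 17 parameters, R²y from 0 to 0.5 (formula).** 69–85% at ICC 0.05 and 81–92% at ICC 0.03. Allowing R²x to vary takes about 2 to 4 points off.

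**6. Low-dimensional alternative at ICC 0.1.** One score term (27 degrees of freedom) gives 87% at R²y = 0 and 94% at R²y = 0.3. Two tercile indicators (26 degrees of freedom) give 85% and 93%.

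**The case against.** Several points on the other side stand.

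- **The size is uncertain.** It depends on the true ICC, which the protocol calls conservative, and on the between-school variance explained. Neither is known, and 48% is the unfavourable corner. With 13 parameters and 70% explained, power is about 91%.
- **17 is a working count.** A region or category absent from the 30 schools drops out; extra levels of school type or religious affiliation would add terms.
- **Adjustment has a purpose.** Policy was not randomised. A propensity score balances covariates on average in large samples. With 10 permissive schools it need not carry all the confounder information, so the choice trades bias against variance, and only the variance is calculated here.
- **Details may sit in an analysis plan that is not shown.** That is true of coding and of the degrees-of-freedom method. The adjustment set itself is stated in the article, as is a power figure that does not belong to it.

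The repeated well-being measure does not rescue the precision. Averaging two measures with an assumed within-pupil correlation of 0.7 adds only 1 to 2 points of power at ICC 0.1 for 0–50% explained, because between-school variance dominates.

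A reader might infer more than the documents support. Near-collinearity is not shown: an expected inflation of 2.4 to 2.7 is a loss of precision. Dependence on one or two unusual schools cannot be judged, since the article does not say how many selective or rural schools are recruited. A raised type I error would require a large-sample z test, and the article specifies none. Nor is the absence of terciles from the analysis a fault in itself, because the score is a function of the variables being adjusted for.

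**Conclusion.** The concern holds as a mismatch between two sections of the article. The sample size arithmetic is correct, but its 90% describes an unadjusted comparison and is not a property of the stated primary model. At the protocol's own ICC, the stated model has about 48, 57, 68 or 80% power at 0, 30, 50 or 70% of between-school variance explained. These figures rest on 17 parameters, equal cluster sizes of 39, a true difference of 3 points and covariates unrelated to policy; real association with policy would inflate the variance further. At ICC 0.03 to 0.05 the shortfall is modest to moderate. It would be too strong to say that the power is certainly lost or that the estimate is biased or unstable: no bias is demonstrated, and a wide interval computed with suitable degrees of freedom would show its own imprecision.

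**What to change.** Reconcile Sample size calculation with Analysis of pupil outcomes:

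- In the primary model, replace the separate school-level variables with the propensity score already estimated on the sampling frame, as one continuous term or as the sampling terciles. A short set of strongly prognostic school covariates may be added if named in advance. Keep the individual-level sociodemographic variables.
- Keep the full 13-variable model as a sensitivity analysis.
- Restate power for the model actually used, over a range of ICC and explained variance.

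The cost is a paragraph of wording and no new data. The downside is that, with few schools, the score may leave some imbalance on individual covariates; the full-model sensitivity analysis would show whether this matters. Keeping all 17 parameters in the primary model at 90% power would instead need about 51, 45 or 39 schools (2:1, ICC 0.1) at 0, 30 or 50% explained.

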#### Analysis of school policies, documents and websites

School policies, documents (eg, school handbook) and relevant website content will be analysed using document analysis.^67^ This will provide an overview of smartphone policy content, rationale and communication and how schools support pupils to use their smartphones and social media, as well as their mental well-being. We will adopt a comparative approach to compare restrictive and permissive policies.

#### Economic analysis

In view of the multiple outcomes of interest, complex nature of school budgets and emergent nature of economic evaluation of school-based interventions, a cost–consequence analysis will be conducted through the relevant data collected (table 3). This approach has been previously employed for school-based interventions.^68^ In addition to the WEMWBS and CHU-9D outcomes, secondary behavioural and health outcomes outlined in the intervention logic model will be included (figure 1). An exploratory cost-utility analysis from the payer (school) perspective will be conducted to compare incremental education costs and incremental Quality-Adjusted Life-Years associated with restrictive daytime smartphone use.

#### Qualitative/case study analysis

Given the purpose of the case study method to understand complexity and situatedness,^69^ coupled with the overarching aim of this study to compare schools that have restrictive and permissive smartphone policies, it seems appropriate to analyse the case study data taking a dual approach. Thus, each case study will be analysed individually using a thematic analysis,^70^ and then multiple case analysis will be adopted.^71^ Following this approach, the findings will then be reported in detailed ‘vertical’ case reports on single schools, and in multiple case thematic analysis.^71^

### Patient and public involvement

During research plan development, a teacher member of the investigator team advised on the study. We also consulted with adolescents and teachers through an online survey (teachers n=40) and five FG consultations (teachers n=11; adolescents n=20). In addition, we undertook analysis of school websites to determine the nature of school smartphone policies. Information gathered through these activities helped to inform and refine the study design, including categorisation of school policy types, research questions, data collection methods, primary and secondary outcomes and the logic model (figure 1).

The approach to PPI during the SMART Schools Study has been constructed based on National Institute for Health Research guidelines.^72 73^ We are engaging with two groups throughout the study: (1) adolescents (from secondary schools); and (2) adults (from schools/teachers, parents/families, local/national health organisations and policy). These groups are directly impacted by the research and are representative of key stakeholders who would act on the findings. We have one PPI lead and a PPI coapplicant, who are leading on PPI activities. Throughout the study there will be four online meetings per group which will focus on: (1) designing and managing study procedures; (2) undertaking the research; and (3) dissemination. The results and conclusions from each PPI group meeting will be reported using Guidance for Reporting Involvement of Patients and the Public (GRIPP2) checklist^74^ for reporting PPI in research.

## Ethics and dissemination

### Ethical and regulatory considerations

Full ethical approval was obtained from the University of Birmingham’s Science Technology, Engineering and Mathematics Research Ethics Committee on 8 July 2022 (ERN_22-0723).

For participation in the study, parents/carers of pupil participants are not asked for active consent but are given the opportunity to complete and return a form to opt their child out of taking part in the study. Pupil, teacher, SLT and parent/carer participants are asked to provide online or written consent (or assent).

We have also developed a safeguarding protocol for conducting research on mental health with adolescents. This safeguarding protocol has been developed in the context of our measure for depression (PHQ-9) that detects whether adolescents in our sample may have had self-harm or suicidal thoughts in the past 2 weeks. The protocol outlines key procedures during recruitment, data collection and debriefing periods to safeguard pupils, and include steps related to confidentiality and establishing efficient, secure and effective communication pathways between the research team and school leaders.

Study sponsorship is provided by the University of Birmingham, with provision of research related costs supported by the National Institute for Health Research (NIHR). Data management and storage is compliant with the University of Birmingham’s policies and procedures. Participant data from online surveys and other sources will be pseudo-anonymised, stored on a University of Birmingham secure server and retained for 10 years through the University’s Research Data Archive. Data from this study will be owned by the University of Birmingham.

Study oversight will be guided by an independently chaired Study Steering Committee (SSC) and a Data Management and Ethics Committee (DMEC). A study monitoring plan has been developed and agreed on by the SSC and DMEC. The current protocol has been reviewed and agreed on by all members of the SSC and DMEC.

### Dissemination

Dissemination activities will be co-produced with our PPI participants. We have planned the following dissemination outputs: policy briefings and research summaries for agencies on the impact of school smartphone policies on adolescent mental well-being; guidelines and resources for schools on the characteristics of school smartphone and social media policy implementation that positively influence mental well-being; blogs, podcasts, videos and infographics to raise awareness and understanding of relationships between smartphones and social media and mental well-being; an NIHR public report that summarises the main project findings; and peer review and open access publications focused on the main study findings.
